### Interventions

2.5

There are different treatments for dry eye including topical medication and surgical intervention. In this study, we choose patients who only received artificial tears with or without a weak steroid, that is, 0.02% fluorometholone before or at the start of treatment at the beginning of the study. We will not change treatment medication until completion of study.

The subjects in each group will undergo 36 sessions of activated LA treatment, thrice a week, for 12 weeks, using a gallium aluminum arsenide LaserPen (maximal power, 150 mW; wavelength, 810 nm; area of probe, 0.03 cm^2^; power density, 5 W/cm^2^; pulsed wave; and Bahr frequencies [B1: 599.5 Hz, B2: 1199 Hz, B3: 2398 Hz, B4: 4776 Hz, B5: 9552 Hz, B6: 19,104 Hz, and B7: 38,208 Hz]; RJ-Laser, Reimers & Janssen GmbH, Waldkirch, Germany). We will use the same acupoints in both the experimental and the sham groups. The subjects in the control group will receive sham LA treatment, without any laser output (no stimulation), while the subjects in the experimental group will sequentially receive 0.375 J of energy at each of the following acupoints: BL2 (Cuanzhu, B3) (Fig. 2), TE23 (Sizhukong, B3), ST2 (Sibai, B3), LI4 (Hegu, B3), ST36 (Zusanli, B2), and GB37 (Guangming, B2) (Fig. 3). The laser treatment will be applied to each point for 5 seconds, to deliver a total treatment dose of 4.5 J/cm^2^. All acupoints are selected and localized according to the WHO Standardized Acupuncture Point Location guidelines.^[16]^ In all the subjects, the laser application will be performed by the same experienced physician who has sufficient training and is a licensed Chinese medicine practitioner in Taiwan. Protective goggle and laser shield were used by the operator and the patient to inhibit visual perception during LA, respectively.

**Figure 2 F2:**
[figure not shown]
Laser acupuncture performed using the LaserPen device at the BL2 acupoint.

**Figure 3 F3:**
[figure not shown]
Acupoints used for dry eye: 1. BL2, 2. TE23, 3. ST2, 4. LI4, 5. ST36, and 6. GB37.

### Outcome measurements

2.6

Both eyes will be assessed for outcomes, 4 and 12 weeks after the first visit. Outcome measurements include 2 aspects, subjective ophthalmologic tests and objective questionnaires for ocular symptoms related to dry eyes. The primary outcome is the difference in the OSDI changes between the 2 groups. The secondary outcomes are the differences in TFBUT, Schirmer I test (with anesthesia) score, and 10-cm visual analog scale (VAS) score of eye discomfort.

OSDI is a 12-item scale for the assessment of symptoms related to dry eye disease and their effects on vision.^[17]^ The scores range from 0 to 100, and higher scores represent a more severe dry eye state. TFBUT measures the time required for tears to evaporate and diffuse after blinking naturally.^[18]^ A Schirmer I test (with anesthesia) is used to assess how quickly the eyes produce tears.^[19]^ A 10-cm VAS (0–10 points, least to greatest discomfort intensity) is used to measure the intensity of eye discomfort. The OSDI and VAS score are assessed by separate outcome assessors who did not perform the LA treatment. TFBUT and Schrmir I test outcomes are evaluated by ophthalmologists.

The reasons for patients not completing the follow-up visits or dropping out of the study, such as adverse events/intercurrent illnesses, suboptimal response to therapy, failure to return for follow-up visits, failure to meet selection criteria at entry, other protocol violations, and refusal to receive treatment, will be recorded. The potential adverse events will also be recorded despite the fact that only 0.375 J will be delivered to an acupoint.

### Statistical analysis

2.7

All data will be presented as mean ± standard deviation. The independent *t* test and chi-square test are used to evaluate and compare the baseline patient characteristics between the experimental and sham groups. Repeated measure analysis of variance and multiple comparisons are used to evaluate the changes in the OSDI, TFBUT, Schirmer I test result, and VAS score between the experimental and sham groups. Differences are considered to be significant at a *P* value of <.05. All analyses are performed with the SPSS for Windows, version 22 (Statistics 22, SPSS, IBM Corp., Chicago, IL).

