**Methods::**

This protocol is a 2-center randomized controlled trial investigating the effect of laser acupuncture on dry eye. Two hundred participants aged 20 to 65 years will be randomly assigned to the experimental group (LA plus conventional treatment) or the sham control group (LA without laser output plus conventional treatment) at 2 clinical research centers in South Taiwan. The subjects will undergo LA treatment thrice a week for 12 weeks. The subjects in the experimental group will sequentially receive 0.375 J of energy at each of the following acupoints: BL2, TE23, ST2, LI4, ST36, and GB37. The subjects in the control group will also receive a sham LA treatment, without any laser output. Outcome assessments will include evaluation of the ocular surface disease index (OSDI), tear film break-up time (TFBUT), Schirmer-I test finding, and the visual analog scale (VAS) score at 4 and 12 weeks before treatment. The OSDI, TFBUT, Schirmer-I test result, and VAS score of the participants will be analyzed and compared between the experimental and control groups using the paired *t* test and one-way analysis of variance.

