### Study design

2.2

This 2-center, randomized, controlled trial is being conducted at the Department of Ophthalmology, Chinese Medicine at the Kaohsiung Chang Gung Memorial Hospital and the Sunming Eye Clinic, 2 clinical research centers in South Taiwan from August 2016 and will continue until July 2018. The participants independently recruited by each center will be randomly allocated to the experimental group (LA plus conventional treatment, n = 100) or the sham control group (LA without laser output plus conventional treatment, n = 100). All participants will receive 36 sessions of treatment over a 12-week period. The study design is depicted in Fig. 1.

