### Sample size and randomization

2.4

The necessary sample size was calculated from the results of a previous study on the effects of acupuncture. The mean difference (standard deviation) of the OSDI after acupuncture treatment was –17.61 (15.61), and after sham acupuncture, was –17.20 (18.81).^[11]^ Anticipating a 15% dropout rate, a total of 200 participants (http://powerandsamplesize.com) were recruited and evenly assigned to each center (100 participants in each center). Participants were randomly allocated to either an experimental or a sham control group using a research randomizer (https://www.randomizer.org). We equally randomized patients who were refractory to conventional treatment and those who were stable and responded to conventional treatment. The trial participants, outcome assessors, and data analysts will be blinded after assignment to interventions using label A and B for the 2 groups.

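### The repeated-measures ANOVA in Section 2.7 has no baseline covariate, so it gives up precision that a baseline-adjusted model would recover from data already collected

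*Protocol article*

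**What the plan says.** Section 2.6 defines the endpoint: "The primary outcome is the difference in the OSDI changes between the 2 groups". On timing it says: "Both eyes will be assessed for outcomes, 4 and 12 weeks after the first visit". It does not say which of the two visits is primary.

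Section 2.7 gives the efficacy analysis: "Repeated measure analysis of variance and multiple comparisons are used to evaluate the changes in the OSDI". The same sentence covers TFBUT, Schirmer I and VAS. Section 2.7 mentions baseline only for comparing patient characteristics between the groups, by independent t test and chi-square test. It does not say whether the repeated measure is the raw score at baseline, week 4 and week 12 or the change from baseline at weeks 4 and 12. Nor does it say which model term is the test.

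The Methods paragraph of the abstract names other tests; outcomes are to be "compared between the experimental and control groups using the paired *t* test and one-way analysis of variance". Neither of these adjusts for baseline.

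**The concern.** The endpoint is a change, so each patient contributes a baseline OSDI. A plan can use that value in three ways: subtract it, enter it as one more level of the time factor, or adjust for it as a covariate. The first two are what a repeated-measures ANOVA of changes normally means. The third is at least as precise for the same contrast, and usually more so.

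The loss matters here because the trial is not large for this outcome. With the change SD quoted in Section 2.4 and the expected completers, an unadjusted week-12 comparison has 80% power only for a difference of about 7.4 OSDI points. The same choice carries over to all three secondary outcomes.

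**Working it through.** **Inputs from Section 2.4.** The OSDI change was -17.61 (SD 15.61) after acupuncture and -17.20 (SD 18.81) after sham in the earlier trial. On numbers: "Anticipating a 15% dropout rate, a total of 200 participants". Hence 200 × 0.85 = 170 completers, 85 per arm. Alpha is 0.05 (Section 2.7), taken as two-sided because the article does not say.

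**Assumed, not in the article.** The correlation r between baseline and follow-up (0.3, 0.5 and 0.7); equal variances and equal correlations over the three visits; the true difference set in step 3.

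**1. The plan's own figure.** Pooled SD = sqrt((15.61² + 18.81²)/2) = 17.28. Difference = 17.61 − 17.20 = 0.41. At 80% power (assumed, as none is stated), n per arm = 2 × (1.960 + 0.842)² × 17.28² / 0.41² = 27,898. The stated 200 is therefore not reproduced from the quoted inputs, and 0.41 cannot serve as the effect for comparing methods.

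**2. Variance at one visit.** With common SD s:
- change score: 2s²(1 − r)
- baseline-adjusted (ANCOVA): s²(1 − r²)
- ratio: (1 + r)/2 = 0.65, 0.75, 0.85 for r = 0.3, 0.5, 0.7

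The direction does not depend on equal variances. With SDs s0 at baseline and s1 at follow-up, the change-score variance minus the adjusted variance is (s0 − r·s1)², which is never negative.

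**3. Power at week 12.** The unadjusted SE is 17.28 × sqrt(2/85) = 2.651. The difference giving 80% power is 2.651 × (1.960 + 0.842) = 7.43 (7.47 with the t distribution). The adjusted SE is 2.651 × sqrt((1 + r)/2), and power is Φ(7.43/SE − 1.96).

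| r | Adjusted SE | Power, change score | Power, adjusted | Difference detectable at 80% power, adjusted |
|---|---|---|---|---|
| 0.3 | 2.138 | 80% | 94% | 5.99 |
| 0.5 | 2.296 | 80% | 90% | 6.43 |
| 0.7 | 2.444 | 80% | 86% | 6.85 |

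**4. The same comparison on the mean of weeks 4 and 12.** Suppose the full 7.43 points is present at both visits. The variance of the mean change is 1.5s²(1 − r), and of the adjusted mean s²[(1 + r)/2 − r²]. Power is 90% unadjusted, against 99%, 98% and 95% adjusted.

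**5. Raw scores with baseline as a time level.**
- *Group-by-time test (2 df):* 83% power if the effect is equal at both visits. If only half of it is present at week 4, power is 70.5%. Neither figure depends on r here, because the change SD is held fixed.
- *Group main effect:* it averages in a visit with no true difference, so a constant effect d is estimated as (0 + d + d)/3 = 2d/3. Power is 86%, 63% and 37% at r = 0.3, 0.5 and 0.7.

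**The case against.** A reader might infer that the planned analysis biases the effect towards zero, or that it cannot answer the primary question. The article supports neither. Dilution needs two things together: baseline as a level of the time factor, and the group main effect as the test. Section 2.7 says neither. Its reference to changes, and the week-4 and week-12 assessments in Section 2.6, fit an analysis of change scores at least as well, and then nothing is diluted. If baseline is a time level, the group-by-time interaction does test whether change differs between arms. It spends 2 degrees of freedom and forgoes the covariate gain, but it is not off target. The multiple comparisons could also supply visit-specific contrasts.

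A reader might also quote a halving of the week-12 effect. That requires assuming that only half the effect is present at week 4. Averaging weeks 4 and 12 alone would then give (0.5 + 1)/2 = 0.75 of it. Including baseline gives (0 + 0.5 + 1)/3 = 0.5, so baseline itself accounts for a one-third reduction.

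It is fair to add that the gain can be modest. With a constant effect, the group-by-time test (83%) is only about 3 points below week-12 ANCOVA at r = 0.7 (86%). Unadjusted mean change over both visits (90%) equals week-12 ANCOVA at r = 0.5. These pairs compare different contrasts, however; for the same contrast, adjustment is never less precise.

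Finally, covariates and covariance structure are often left to an analysis plan, and a journal article is condensed. That would answer a complaint about missing detail. Here the article does state a method, and a better one is available from the same data.

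**Conclusion.** The point holds as a matter of efficiency, not validity. The stated analysis leaves out a covariate that the trial has. The cost at a single visit is a variance 1/0.85 = 1.18 to 1/0.65 = 1.54 times that of the adjusted analysis, for r from 0.7 to 0.3. From an 80% base this amounts to 6 to 14 percentage points of power.

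The figures rest on the assumed r, on equal variances and correlations over time, on 85 completers per arm, and on a difference of about 7.4 points chosen to give 80% power. That difference is not a figure from the article. Only the direction of the result is free of these assumptions.

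Baseline adjustment does not rescue the sample size. At the quoted 0.41-point difference it would still need 27,898 × 0.65 = about 18,100 per arm at r = 0.3, or 27,898 × 0.85 = about 23,700 at r = 0.7. The change is worth making, but it is not critical.

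**What to change.** In Section 2.7, replace the repeated-measures ANOVA with a mixed model for the week-4 and week-12 values. Include arm, visit, arm-by-visit, baseline value and baseline-by-visit, with an unstructured covariance. Name one arm contrast in advance as the primary estimate, for example week 12, the end of treatment, and report it with a 95% CI. Use the same model for TFBUT, Schirmer I and VAS, each with its own baseline. Bring the abstract into line with it.

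Naming the visits, the covariate and the contrast also removes the doubt about the time levels and the decisive term. The cost is one paragraph of Section 2.7 and one sentence of the abstract. No new data are needed, and the model runs in the MIXED procedure of the software already named. The sample-size calculation in Section 2.4 needs its own correction.

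### Repeated-measures ANOVA in its classical form would make the primary OSDI comparison a completer analysis at the expected 15% dropout, unless missing data are handled elsewhere

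*Protocol article*

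**What the plan says.** The protocol article defines the endpoint in section 2.6: "The primary outcome is the difference in the OSDI changes between the 2 groups". Outcomes are assessed 4 and 12 weeks after the first visit.

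Section 2.7 names the method: "Repeated measure analysis of variance and multiple comparisons are used to evaluate the changes in the OSDI", and likewise in the three secondary outcomes. On software it adds "All analyses are performed with the SPSS for Windows, version 22". It names no SPSS procedure, analysis set or missing-data method.

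Section 2.4 sets the expected loss: "Anticipating a 15% dropout rate, a total of 200 participants" are recruited. Section 2.6 lists reasons for non-completion to be recorded. Besides adverse events, intercurrent illness and refusal of treatment, they include "suboptimal response to therapy, failure to return for follow-up visits, failure to meet selection criteria at entry, other protocol violations".

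The Methods part of the abstract describes a different analysis, in which the outcomes are "compared between the experimental and control groups using the paired *t* test and one-way analysis of variance".

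**The concern.** Classical repeated-measures ANOVA needs a complete set of visits for each participant. Someone with OSDI at baseline and week 4 but not at week 12 contributes nothing, and the week-4 value already collected is discarded. The same happens to someone who misses only week 4.

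The article combines this method with a dropout rate that it predicts itself and with at least one dropout reason tied to the outcome. If poor responders leave at different rates under laser and sham, the completers are no longer the groups that were randomised. The difference in OSDI change then partly reflects who stayed. The error flatters the arm that loses more of its poor responders. There is also some loss of precision.

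**Working it through.** **Inputs.** From section 2.4: SD of OSDI change 15.61 (acupuncture) and 18.81 (sham) in the earlier acupuncture study; dropout 15%; total 200. From section 2.2: 100 per arm. From section 2.7: significance at 0.05, taken as two-sided. Assumptions not in the article: 80% power, dropout by arm, the correlation ρ between week-4 and week-12 OSDI change (0.5 or 0.7), and how strongly dropout depends on response.

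**1. The article's dropout allowance.** 200 × 0.85 = 170 completers, and 170/0.85 = 200. The allowance is internally consistent: about 30 participants lost and about 85 per arm left. (Whether 170 follows from the quoted OSDI results is a separate matter, not used here.)

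**2. Precision.** Pooled SD = √[(15.61² + 18.81²)/2] = 17.28. Detectable difference = (1.960 + 0.842) × 17.28 × √(2/n):
- n = 100 per arm: 6.85 points
- n = 85 per arm: 7.43 points

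Listwise deletion costs at most about 0.6 points of detectable difference. The 15% allowance already covers this.

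**3. Bias when dropout depends on observed week-4 OSDI.** Take no true effect, and dropout of 20% in one arm and 10% in the other (15% overall). If the leavers are exactly the worst week-4 responders, the completer mean at week 12 shifts by ρ × SD × φ(z)/(1 − p), where p is the dropout proportion and z the matching normal cut-off.
- p = 0.20: φ(z)/(1 − p) = 0.350
- p = 0.10: φ(z)/(1 − p) = 0.195
- difference 0.155; × 17.28 = 2.68 points
- × ρ = 0.5: 1.3 points; × ρ = 0.7: 1.9 points

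Selection is rarely that sharp. A large-sample simulation (2 million per arm) instead let the chance of dropout rise smoothly with a poor week-4 response (logistic slope 0.7 or 1.5 per SD). Bias in the completer difference:

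| Dropout by arm | Bias, OSDI points |
|---|---|
| 15% / 15%, same dependence on response | about 0 |
| 10% / 20% | 0.5 to 1.2 |
| 5% / 25% | 1.1 to 2.6 |

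For a 10%/20% split, the two calculations together give roughly 0.5 to 1.9 points. If dropout is unrelated to response (slope 0), the bias is about 0 whatever the split.

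**4. What a mixed model would recover.** In every scenario of step 3, an estimate that keeps the dropouts' week-4 data has bias of about 0. The result differs when dropout depends on the week-12 value that is never seen. If the leavers at 20%/10% are exactly the worst week-12 responders, the completer bias is the full 2.7 points, and an estimate using all week-4 data still leaves about 1.9 to 2.3 of it. If dropout correlates only 0.5 with the week-12 outcome, the completer bias is 1.3 points and roughly 0.7 to 1.0 remains.

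**The case against.** The strongest objection is that the article never says incomplete cases are excluded. Listwise deletion is general knowledge about the classical procedure, not a statement in the document. SPSS 22 also has a mixed-model procedure. Analysis sets and missing-data rules are commonly left to a full protocol or analysis plan, and neither is shown. This stands, and it is why the point is conditional. A reader might infer that the primary result is certain to be a completer comparison, and the documents do not support that. What remains is that the method actually named is ANOVA, which ordinarily means the complete-case form.

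Second, the abstract's paired *t* test and one-way ANOVA mean that the primary analysis is not uniquely fixed. A one-way ANOVA at a single visit would keep a person who missed only the other visit. That is correct, but a week-12 change score still omits anyone without a week-12 value, so the conflict adds a reason to edit and does not remove the problem.

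Third, section 2.6 is a list of reasons to record. A reader might take it to mean that ineligible or non-adherent participants are removed from the analysis. It says no such thing, and several reasons on it need not relate to outcome.

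Fourth, a reader might take 2.7 points as the harm that a mixed model would cure. It is not: that figure assumes dropout determined by the unseen week-12 value, and the mixed model leaves most of that bias in place.

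**Conclusion.** The point holds in conditional form. Run classically, the named method would use about 170 of 200 participants, or fewer if some people miss a single visit and return. The primary comparison would then be a completer analysis unless another document provides for missing data.

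The bias that the proposed change of method would remove is roughly 0.5 to 1.9 OSDI points at an assumed 20% versus 10% dropout that depends on week-4 OSDI. It is about 0 if dropout and its dependence on response are the same in both arms. Neither size nor direction can be read from the article, which gives no dropout by arm. For scale, the detectable difference is about 7.4 points at 85 per arm, so the plausible bias is modest but not negligible. The precision loss is minor and already planned for. The change should be made because it protects the primary comparison at little cost; nothing here shows that the result will be biased.

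**What to change.** In section 2.7, replace repeated-measures ANOVA with a likelihood-based mixed model for repeated measures, which the MIXED procedure in SPSS 22 can fit. Include treatment, visit and treatment-by-visit terms. Analyse all randomised participants in their assigned arm with every available OSDI value, and report the week-12 contrast. Change the abstract so that it names the same analysis.

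The mixed model does not remove bias when dropout depends on the unobserved week-12 outcome. Add one sensitivity analysis that assumes worse outcomes for dropouts.

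If a full protocol or analysis plan already provides for missing data, one sentence in section 2.7 pointing to it would settle the main concern.

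The cost is a few lines of text and slightly more analysis work, with no new software or patients. A rule against removing participants after randomisation is not part of this change, because the article states no exclusion rule to correct. Nor is OSDI collection after treatment stops, because that would add follow-up.

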### Data monitoring

2.8

Data monitoring committee (DMC) is not needed because laser acupuncture is general practice and noninvasive intervention.

## Discussion

3

The prevalence of dry eye in the Taiwan population is 4.87%, and the ratio of affected women to men is 2.34.^[20]^ Two key mechanisms are thought to cause dry eye: tear hyperosmolarity and tear film instability, both of which are generally related to ocular surface inflammation.^[1]^ The therapy for dry eye traditionally involves hydrating and lubricating the ocular surface, which may provide temporary relief from the symptoms of irritation and blurred vision.^[21]^ It is important to educate the patients and make them aware that dry eye is a chronic disease that needs long-term treatment, and that evident therapeutic effects can be observed only after a certain period. Treatment for dry eye disease involves a step ladder approach that is based on the severity of the condition.^[22]^

It is thought that acupuncture might help reduce inflammation through modulation of vagus nerve activity,^[23]^ by regulating the anti-inflammatory pathways in the ocular surface or other accessory organs of the eye. The analgesic effects of acupuncture, which alleviate ocular irritation and pain, might also contribute to its therapeutic effects.^[24]^ Prior studies have shown that acupuncture can modulate the autonomic nervous and immune systems, to increase lacrimal secretion by stimulating lacrimal gland function.^[25–28]^ In comparison with traditional acupuncture for obtaining qi, laser acupuncture is not related to somatosensation but has the advantage of being noninvasive and aseptic. Laser acupuncture is also effective and needs less time than traditional acupuncture. Furthermore, there is no heat generated during the procedure that make laser acupuncture painless and safe.^[29]^ LA integrates the positive effects of both acupuncture and low-level laser therapy.^[15]^

In conclusion, laser acupuncture is expected to be effective for the treatment of dry eye in addition to conventional treatments.
